**Fig. 2 Fig2:**
[figure not shown]
Bone grafts in the intervertebral cage. For each cage, one space will be filled with a bone graft with PRP, and the other will be filled with a bone graft without PRP

Our primary endpoint is the interbody fusion rate at 1 year after surgery. Plain radiographs and computerized tomography (CT) multi-planar reconstruction coronal and sagittal images will be obtained for the evaluation of interbody fusion at 1 year after the surgery. Trabecular bone continuity between the grafted bone within the window of the cage and vertebral endplates will be evaluated by three spinal surgeons. Interbody fusion will be determined when no instability is identified in flexion–extension radiographs, and bony continuity will be identified in at least one sagittal or coronal slice of CT multiplanar reconstructed images [2].

The secondary endpoints are as follows: (1) the interbody fusion rate at 6 months after surgery; (2) temporal changes in grafted artificial bone such as resorption and remodeling; (3) bony contact between the cage and vertebral endplates; and (4) visual analog scale (VAS), Japanese Orthopedic Association Back Pain Evaluation Questionnaire (JOA-BPEQ), Oswestry disability index (ODI), and European Quality of Life 5 dimensions (EQ-5D).

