### Design of the study

The study is a prospective controlled superiority trial study with randomly allocated groups.

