**Fig. 1 Fig1:**
[figure not shown]
Schematic diagram showing the trial timeline. Consecutive patients scheduled for lateral lumbar interbody fusion will be recruited for this study. Whole blood will be drawn from each patient to prepare platelet-rich plasma. In an intervertebral cage, one space will be filled with a bone graft impregnated with platelet-rich plasma, and the other will be filled with a bone graft without PRP

GPS® III (Zimmer Biomet, Warsaw, IN, USA) will be used to prepare a PRP. A total of 52 mL of peripheral blood will be drawn from each patient before the surgery. The withdrawn blood will be centrifuged for 15 min at 3200 rpm. After elimination of platelet-poor plasma, PRP will be obtained by extracting the buffy coat layer.

CoRoent XL PEEK cage® (NuVasive, San Diego, CA, USA) will be used as an intervertebral fusion cage for the LLIF. A block-type Affinos® will be used as a bone graft in the intervertebral cage. Each cage has two spaces for a bone graft; one space will be filled with an artificial bone block impregnated with PRP, and the other will be filled with an artificial bone block without PRP (Fig. 2). Therefore, two artificial bone blocks can be grafted at each intervertebral level. The side of the bone graft with PRP will be alternately set in the order of insertion. In this way, we will assign interventions (bone graft with PRP) and controls (bone graft without PRP) randomly.

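### No masking of the CT fusion readers to the PRP side is described, and the alternating side rule makes the side inferable to anyone who knows the sequence

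*Protocol article*

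**What the plan says.** All of this is in the protocol article, mostly under Study procedures.

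- **Endpoint:** "Our primary endpoint is the interbody fusion rate at 1 year after surgery".
- **Readers:** "Trabecular bone continuity between the grafted bone within the window of the cage and vertebral endplates will be evaluated by three spinal surgeons".
- **Criterion:** it has two parts. The first is dynamic radiographs: "Interbody fusion will be determined when no instability is identified in flexion–extension radiographs". The second is CT: "bony continuity will be identified in at least one sagittal or coronal slice of CT multiplanar reconstructed images".
- **Side of PRP:** each cage has two spaces, one with PRP and one without. "The side of the bone graft with PRP will be alternately set in the order of insertion". The next sentence calls this random: "In this way, we will assign interventions (bone graft with PRP) and controls (bone graft without PRP) randomly".
- **Design statement (Design of the study):** "The study is a prospective controlled superiority trial study with randomly allocated groups". It contains no masking term.

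No section mentions blinding, concealment of the side, or readers separate from the operating team. It is not stated how three differing readings are combined. The only independence provision, under Data management, concerns data monitoring and not image reading.

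**The concern.** PRP and control lie in the same cage and appear on the same CT, so a reader judges them side by side. The judgement is visual and the CT threshold is low: continuity in a single slice is enough. A reader who expects PRP to work, and who knows or can work out which space holds it, may search that space harder and call it fused more readily.

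Any such difference goes straight into the only treatment contrast and would look like a PRP effect. Reanalysis of the same readings could not separate the two. The 6-month fusion rate and the graft-remodelling endpoint are also imaging assessments and may be exposed in the same way. The Discussion presents the trial as confirmatory and as possible support for an alternative to autologous graft, so the reading procedure carries much of the weight.

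**Working it through.** **1. Which component can separate PRP from control?** Absence of instability on flexion-extension films is a property of the level, so both spaces of a cage receive the same result. CT continuity is judged for each space. Within a cage, a difference in fusion status can therefore come only from the CT judgement. The shared criterion also sets a limit: at an unstable level neither space can count as fused, however the CT is read.

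**2. What does alternation reveal?** If sides alternate by insertion order, the side at insertion k fixes the side at k+1, k+2 and so on. Two facts are needed: one known side and the insertion order. The article gives neither the starting side nor whether alternation restarts with each patient. Members of the operating team would have these facts; an outside reader might not.

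**3. The plan's own figure.** Inputs from Sample size estimation: 70.9%, 94.5%, 80% power, two-sided 5%. The pooled formula without continuity correction is

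n = [1.96·√(2p̄(1−p̄)) + 0.842·√(p₁(1−p₁)+p₂(1−p₂))]² / (p₂−p₁)²

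With p̄ = 0.827 this gives 39.1, rounded up to 40 per group, as stated. Power at 40 is 80.9%. Masking changes none of this.

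**4. Size of a reading shift (illustration).** Assume no true effect, a true rate of 70.9% in both groups, n = 40 per group, and the unpaired chi-square test in Statistical analyses. The shift d is an assumption; the document gives no misreading rate.

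Rejection probability = Φ[(d − 1.96·SE₀)/SE₁] + Φ[(−d − 1.96·SE₀)/SE₁], where SE₀ = √(2p̄(1−p̄)/40) and SE₁ = √([p_C(1−p_C)+p_T(1−p_T)]/40).

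| Shift | Read control / PRP | SE₀ | SE₁ | Rejection |
|---|---|---|---|---|
| 10 points, PRP only | 70.9% / 80.9% | 0.0956 | 0.0950 | 18.0% |
| 10 points, split | 65.9% / 75.9% | 0.1016 | 0.1010 | 16.5% |
| 15 points, PRP only | 70.9% / 85.9% | 0.0920 | 0.0905 | 36.9% |
| 15 points, split | 63.4% / 78.4% | 0.1016 | 0.1002 | 31.2% |

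Nearly all of these rejections favour PRP.

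**5. How much misreading does that take?** If only unfused PRP spaces are upgraded, 10 points means misreading 10/29.1 = 34% of them, and 15 points means 15/29.1 = 52%. If fused controls are also downgraded at the same rate b, the shift is b(0.291 + 0.709) = b, so a 10% rate gives 10 points.

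| Misreading rate | Upgrade PRP only | Upgrade PRP and downgrade control |
|---|---|---|
| 5% | 5.2% | 7.7% |
| 10% | 6.0% | 16.0% |
| 20% | 9.0% | 47.5% |
| 30% | 14.6% | 81.4% |

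Entries are rejection probabilities under the same assumptions.

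**6. Dependence within a cage.** Steps 4 and 5 treat the two spaces as independent. With an assumed within-cage correlation of 0.5, simulation of the same test gives 8-10% for a 10-point shift and 24-32% for 15 points. The unpaired test is then conservative when there is no bias: its critical value is in effect 1.96/√(1 − 0.5) = 2.77, a rejection rate of about 0.6%. The absolute rates fall, but bias still raises them well above that base. Clustering of levels within patients is ignored throughout.

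**The case against.** The strongest objection is that the point rests on silence. This is a journal article; the full protocol is not shown and may already provide for masked reading. A reader might infer that the surgeons are unmasked, that they operated on these patients, or that they have the operative records. The text says none of this. That objection stands, and the claim is limited to masking not being described. It does not dispose of the point: the article does fix the readers, the criterion and a predictable side rule, and that rule would weaken masking even if masking were intended.

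A reader might also infer that any reader can deduce the PRP side from the scan. That is too strong, because the insertion order and one side must be known as well.

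Nor is a single favourable CT slice enough to call a space fused. The level must also show no instability, which caps the possible bias. Three readers may dampen one reader's expectation, although no rule for combining them is given.

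On size, the arithmetic holds, but the shifts are assumptions, upgrading alone would need a large share of misreadings to reach them, and within-cage correlation lowers the rates. The illustration shows what could happen; it does not predict it.

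Finally, the harm need not be permanent. Biased readings cannot be repaired by analysis, but stored scans can be read again under masking.

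**Conclusion.** The point holds in limited form and should be acted on. As written, the primary endpoint depends on a visual judgement by surgeons for whom no masking is described, under a side rule that is predictable to anyone who knows the sequence. That judgement is the only component that can distinguish PRP from control within a cage.

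The document does not show that bias will occur or how large it would be. The rates of about 16-18% (10-point shift) and 31-37% (15-point shift) rest on assumed shifts, a null rate of 70.9%, 40 spaces per group and independent spaces; they are lower under positive within-cage correlation. If the full protocol already masks the readers, a sentence saying so settles most of the point, and what remains is the predictable side rule.

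**What to change.** - State that the three readers are masked to the PRP side and have no access to operative records or the allocation sequence.
- Give them de-identified CT images cropped to the cage, in random order, with the two spaces under random labels or randomly mirrored. Cropping matters because surrounding anatomy could reveal a mirrored image.
- Have each surgeon read independently, take the majority of three as the primary result, and unmask only after database lock.
- Re-read CTs already acquired in the same way.
- For any remaining levels, set the side by a concealed random sequence instead of alternation.

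The cost is some image-preparation work by the data manager. No extra readers or scans are needed, and the sample size is unchanged.

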### Inclusion criteria

The inclusion criteria are as follows: (1) patients who are scheduled for LLIF for a lumbar degenerative disease; (2) patients who are scheduled for LLIF between 1 and 4 intervertebral levels; (3) patients aged > 20 years; and (4) patients who agree to participate in the current trial and from who informed consent has been obtained both orally and in writing.

### Exclusion criteria

Exclusion criteria are as follows: (1) patients with a history of lumbar surgery, infectious spondylitis, and spinal tumor; (2) patients administered another trial drug within 3 months before the commencement of this study; (3) patients with comorbidities, such as abnormal bone metabolism and hemodialysis, that cause inferior osteogenic ability; (4) patients with uncontrolled diabetes mellitus; (5) patients with anemia (hemoglobin < 9.0 g/dL); (6) patients with hematological disorders; (7) patients who are pregnant or nursing; (8) patients with metallic allergies; and (9) patients who cannot provide a written consent.

### Relevant concomitant care and interventions

Intervertebral cages other than those mentioned above will not be used in the trial. No provision regarding the screws and rods for posterior fixation has been set.

### Criteria for discontinuing the trial

Participation of patients in this trial will be discontinued in the following cases: (1) when the patient declines participation in this trial or withdraws consent; (2) when the patient is found to be ineligible for participation; (3) when it is difficult to continue the trial owing to the onset of a new disease; (4) when the patient’s compliance is poor; (5) when the trial itself is discontinued; and (6) when the patient is determined to be ineligible by the doctor for any other reason.

### Missing data and data from participants who discontinue

All patients will be followed up as per the normal postoperative course, ensuring necessary data acquisition for the research. Additionally, to avoid missing data and to promote participant retention, data managers will announce the required tests, questionnaires, and their schedules to attending doctors and patients. Missing data will not be supplemented, and rejected data will be excluded.

### Data management

The personal information of patients, including medical information, will be handled in accordance with the privacy policy of the regenerative medicine provider. Each patient will be issued an ID that will permit tracing of the patient but will also protect their personal identification information using a strictly monitored ID management system.

Data managers will use the case report system to enter data. The case report system will include paper media and an electronic data capturing system. Study coordinators will verify the accuracy of data entry and check for the presence of missing data. An independent data monitoring manager, with no conflict of interest in this study will be responsible for data monitoring at the primary level.

All investigators will minimize the risks of potential adverse events. All related adverse events will be documented, and appropriate treatment will be immediately provided. An interim analysis will not be conducted.

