**Discussion:**

This trial will verify the efficacy of platelet-rich plasma with Affinos® for bony fusion in lateral lumbar interbody fusion. It will also provide substantial evidence for the effectiveness and safety of platelet-rich plasma in spinal fusion surgery.

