### Sample size estimation

The target sample size for this study is 15. Since patients will individually undergo LLIF at 1 to 4 intervertebral levels, more than 40 intervertebral levels are expected to be included in this study. Therefore, at least 80 bone graft spaces will be included to evaluate bony fusion.

A sample size calculation was performed based on the results of previous studies [2, 12]. In previous studies, the fusion rate of LLIF with Affinos® was 70.9%. And, the intervertebral fusion rate with autologous iliac crest bone was 94.5%. Based on these parameters, we calculated a sample size of 40 bone graft spaces per group with a power of 80% and an alpha of 5% (two-tailed).

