### Patient informed consent

All patients will be given written explanatory materials and consent forms. The principal investigator will provide patients with sufficient information before obtaining informed consent.

This study will be covered by clinical research insurance. Compensation will be provided to the participants who present with adverse events related to the administration of regenerative medicine in this trial.

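### The only adverse-event recording rule stated covers 'related' events, which cannot support the article's claim of substantial evidence on the safety of PRP

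*Protocol article*

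**What the plan says.** Adverse events are handled in two sentences under Methods, Data management. Investigators are to minimise risk, and then "All related adverse events will be documented, and appropriate treatment will be immediately provided". The word 'related' is not defined there. The nearest wording is under Patient informed consent, where compensation is offered for "adverse events related to the administration of regenerative medicine in this trial", but that is a condition for compensation and not a recording rule.

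The Discussion paragraph of the Abstract says of the trial: "It will also provide substantial evidence for the effectiveness and safety of platelet-rich plasma in spinal fusion surgery".

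Under Study procedures, for each cage "one space will be filled with an artificial bone block impregnated with PRP, and the other will be filled with an artificial bone block without" it. Every participant is therefore exposed. The same section gives four groups of secondary endpoints, opening with "The secondary endpoints are as follows: (1) the interbody fusion rate at 6 months after surgery" and continuing with graft changes, cage–endplate contact and patient-reported scores. None is an adverse-event endpoint. On patient numbers, Sample size estimation states: "The target sample size for this study is 15".

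**The concern.** A safety statement needs a count of events that does not depend on what the investigator believed caused them. The usual order is to record the event and then judge its relationship. As worded, the rule makes relationship the condition for recording.

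The design makes that judgement hard. Exposure is universal and known, no patient goes without PRP, and each cage holds both kinds of graft, so a local event at a level may not be separable into a PRP part and a procedure part. An assessor can readily attribute a wound infection, a haematoma or a neurological event to the surgery. If 'related' means related to PRP, the rule then does not require that event to be documented.

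What is at stake is the safety conclusion. The recorded count could be too low, and a later reader could not re-examine causality for events that were never entered.

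**Working it through.** **The plan's own figure.** The article gives no safety calculation. Its one calculated figure is 40 graft spaces per group, for the fusion comparison (70.9% against 94.5%, two-sided 5%, power 80%). With pooled variance and no continuity correction:

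- Mean proportion: (0.709 + 0.945)/2 = 0.827.
- n = [1.960·√(2·0.827·0.173) + 0.842·√(0.709·0.291 + 0.945·0.055)]² / 0.236² ≈ 39.1, rounded up to 40.
- Power at 40 per group is 80.9%.

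The figure reproduces, and nothing in this point depends on it.

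**The passages side by side.**

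1. Recording rule (Data management): related events. No other section says that all events are recorded first and attributed afterwards.
2. Claim (Abstract, Discussion): substantial evidence on safety.
3. Exposure (Study procedures): "one space will be filled with an artificial bone block impregnated with PRP" in each cage, so exposed patients = 15 and unexposed patients = 0. Concealing which space holds PRP would not hide exposure for a patient-level event.
4. Endpoints and tests (Study procedures; Statistical analyses): no adverse-event endpoint or safety comparison appears, so the adverse-event record is the only stated adverse-event source for the claim.

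**Direction of the error.** Let p be a patient's true risk of an event type and r the share of such events judged related and therefore recorded. The recorded risk is p·r. Since r ≤ 1, the filter can lower the count or leave it unchanged. The documents give no value for r.

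**Illustration of the filter (p and r are assumptions).** The probability of recording at least one event in 15 patients is 1 − (1 − p·r)^15.

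| p | r = 1 | r = 0.75 | r = 0.5 | r = 0.25 |
|---|---|---|---|---|
| 10% | 79% | 69% | 54% | 32% |
| 20% | 96% | 91% | 79% | 54% |

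For example, with p = 0.10 and r = 0.5: 1 − 0.95^15 = 0.537.

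**What 15 patients can show with complete recording (no filter).** With 0 events in 15, the one-sided 95% upper limit solves (1 − p)^15 = 0.05, so p = 1 − 0.05^(1/15) = 18.1%. The two-sided 95% limit is 1 − 0.025^(1/15) = 21.8%. These figures come from the number of patients and say nothing about the effect of the filter.

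**The case against.** The strongest reply is that the sentence does not say unrelated events go unrecorded. It states what will be documented and is silent on the rest, and 'related' could mean related to trial participation, the operation included. On that reading infection, haematoma and neurological events after surgery are covered. The text is also a journal article. The full protocol, or the regenerative medicine provision plan mentioned under Confirmation of implementation, may hold a broader rule. Collection window, seriousness grading and similar details are commonly left to such documents, and their absence here is no fault.

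Much of this stands. A reader might infer that unrelated events are definitely discarded, but the article does not say so. It supports only the statement that the single rule given is limited to related events and leaves the word open. That remains a defect of what is stated.

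A reader might also infer that any local complication could vanish from the data. Cage subsidence would be a poor example. The planned radiographs and CT, and the endpoints on graft change and cage–endplate contact, are collected whatever the attribution and would show it at least in part. Symptomatic worsening would partly appear in the patient-reported scores. None of these replaces an adverse-event record for infection, haematoma or neurological events.

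Finally, no safety test is planned, so no planned comparison is biased. That is correct. The issue is possible undercounting behind a claim made in the Abstract.

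**Conclusion.** The point holds in limited form. The only recording rule the article states is restricted to events judged related, the term is undefined, and the judgement is made with exposure known and without a comparator. That rule cannot support a claim of substantial safety evidence, because it can undercount events and prevents later reassessment of those left out.

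The size of the undercount is unknown. The table of probabilities rests on assumed risks and assumed related shares, and shows only how a filter could act in 15 patients. It would be tempting to cite the 18% limit as the damage done by the rule, but it applies with every event recorded. What it supports is a separate statement: the safety claim is too strong for 15 patients even with complete recording.

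The primary endpoint and the listed secondary endpoints are unaffected. The conclusion assumes that the full protocol does not already require recording regardless of attribution. If it does, the article's sentence misstates the protocol and should still be corrected.

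**What to change.** Under Data management, change the opening of the sentence so that it covers *all adverse events, regardless of judged relationship*, and record relationship as a separate field, stating what it refers to (PRP, the operation or trial participation). In the Discussion paragraph of the Abstract, limit the safety claim to a descriptive summary in 15 patients who all received PRP.

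The cost is a small wording change in two places and slightly more case-report entry. No extra visits or patients are needed. The safety claim becomes weaker, which fits what the design can deliver. Attribution will still be made with exposure known and no PRP-free patients, but every event will be available for reassessment.
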